### 4.2. Outcomes

The primary outcomes of this study are the scores on the cognitive tasks and the scores on the gait and balance efficiency scales.

The secondary outcomes are the scores on the self-perception of cognitive deficits scale and on the self-perceived quality of life through the WHO-DAS.

The outcomes will be considered at T1 and T2.

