## 2. Materials and Methods

### 2.1. Aim, Design and Setting of This Study

This study has the following primary objectives:Compare three forms of rehabilitation—cognitive, motor and combined (cognitive–motor)—in three groups of MS patients.Check whether a combined rehabilitation approach can induce a significantly greater improvement on memory efficiency of MS patients, than cognitive rehabilitation performed alone.

Secondary objectives:Evaluate whether self-perception and objective improvement correspond.Evaluate the impact of each rehabilitation program on patients’ overall disability.Monitor the effects of the three rehabilitation conditions after 6 months.

This study will be a single-blind parallel controlled clinical trial, in which each subject will be randomly assigned to a single treatment. The study protocol will be divided into an initial evaluation by standardized tools of clinical, cognitive, emotional, quality of life and functional self-perception state, at time 0 (T0). Subsequently, patients will be assigned to one of the three conditions and will undergo rehabilitation treatment for a total of 12 weeks (two sessions each week). At the end of the treatment, each patient will undergo an overall re-evaluation (T1) with parallel forms of the tools used at T0. After 6 months, all patients will be submitted to a further overall re-evaluation as a follow-up measurement of each treatment (T2). The examiner carrying out pre- and post-treatment evaluations will be different from the one carrying out the rehabilitation process in order to avoid any individual bias. Figure 1 shows the study flowchart.

Patients in charge of both the “Santa Lucia” Neuroscience and Rehabilitation Foundation (Rome) and the “Filippo Turati” Foundation (Rome) will be recruited. All evaluations and rehabilitation training will be conducted at the laboratory and in the rehabilitation sites of the two centers by adequately trained neurologists/physiatrists, psychologists and physiotherapists.

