### 2.3. Assessment Procedures

At T0 all patients will undergo the following assessments:Accurate collection of personal, anamnestic and clinical information;Expanded Disability Status Scale (EDSS) [24]: is a rating scale administered by a trained physician, aimed at evaluating functional CNS sub-systems. EDSS is used also to identify disease progression in MS patients and to evaluate the effectiveness of therapeutic interventions in clinical trials. It consists of an ordinal classification system ranging from 0 (normal neurological status) to 10 (death for MS) in increments of 0.5 (when EDSS 1 is reached). The lower values of the EDSS scale measure deficits based on neurological examination, while the upper range of the scale (>EDSS 6) measures the handicaps of MS patients [25]. The determination of the 4–6 interval of the EDSS strongly depends on aspects concerning walking [25].Neuropsychological evaluation through the Minimal Assessment of Cognitive Functioning in Multiple Sclerosis battery (MACFIMS) [26], in the Italian version [27]. This battery consists of seven tests:

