## 4. Statistics and Outcome

### 4.1. Data Analysis

The sample size has been determined based on an a priori power analysis, using the software G*Power 3.1 [56], with a 0.30 effect size, power of over 0.95, and an alpha level of 0.05, as being sufficient for both repeated measures, within–between interaction Analysis of Variance (ANOVA). The minimum number of participants required is 48 (16 participants for each group), but we have decided to reach a total number of 60 participants (20 participants for each group) in order to avoid possible drop-out effects.

For the purposes of this study, different types of statistical analysis will be carried out using SPSS 18 (SPSS Inc., Chicago, IL, USA) and a significant threshold throughout this study will be set at *p* < 0.05.

Statistical analysis will be of two types:“Within-group” analyses. These statistical analyses will be aimed at evaluating any improvement in patients’ cognitive performance. Within each group of patients, the assessments at T0 will be compared with that at T1 and T2 through a repeated measures ANOVA between the scores of the cognitive assessments. In case of significance, post hoc tests will be carried out to which a Bonferroni correction will be applied with significance set at *p* < 0.016. Similarly, the same analysis will be conducted to compare the levels of anxiety and depression, the self-perception of cognitive deficit and the level of perceived disability.“Between-group” analyses. These statistical analyses will be aimed at comparing the results obtained by the groups at T0, T1, and T2 by performing an ANOVA between the scores of the cognitive assessments. In case of significance, post hoc tests will be performed to which a Bonferroni correction will be applied with significance set at *p* < 0.016. Additionally, in this case, the same comparative analysis will be carried out on the following variables: levels of anxiety and depression, self-perception of one’s cognitive difficulties and level of perceived disability.

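### All cognitive, gait and balance scores are primary at T1 and T2, each tested at p<0.05, with no lead endpoint and no control of error across them

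*Protocol article*

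**What the plan says.** Section 4.2 defines the primary outcomes as a set: "The primary outcomes of this study are the scores on the cognitive tasks and the scores on the gait and balance efficiency scales". It adds "The outcomes will be considered at T1 and T2", without ranking scores or visits.

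Section 2.3 describes the cognitive battery ("This battery consists of seven tests"), several of which give two scores, and separately the walking and balance measures.

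Section 4.1 gives one error level: "a significant threshold throughout this study will be set at" p<0.05. The between-group analysis is described as "comparing the results obtained by the groups at T0, T1, and T2 by performing an ANOVA between the scores of the cognitive assessments". The only correction follows: "In case of significance, post hoc tests will be performed to which a Bonferroni correction will be applied with significance set at" p<0.016, which is 0.05/3 and so matches three pairwise comparisons. The within-group analysis is additional: "Within each group of patients, the assessments at T0 will be compared with that at T1 and T2 through a repeated measures ANOVA".

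Section 2.1 lists two primary objectives. The first compares the three programmes and names no outcome. The second is the only one that names an outcome: "Check whether a combined rehabilitation approach can induce a significantly greater improvement on memory efficiency of MS patients, than cognitive rehabilitation performed alone". The six-month effects are a secondary objective there.

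**The concern.** When many outcomes are all primary and each is tested at 0.05, the chance that at least one is significant by accident is well above 0.05. The 0.016 threshold does not help with this. It deals with which pair of arms differs once a given score has shown a significant ANOVA, not with how many scores were tried.

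The discussion (section 6) says that positive results could support a change in clinical practice. As written, one significant score out of up to 30 tests could be reported as a primary success, and nothing in advance says which score at which visit answers the question. The sample size was calculated for one test at alpha 0.05, so it does not reflect this family either.

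**Working it through.** **1. The plan's own figure.** Section 4.1 gives effect size f = 0.30, power over 0.95, alpha 0.05, minimum N = 48. For a within–between interaction with k = 3 groups and m measurements, λ = f²·N·m/(1−ρ), df1 = (k−1)(m−1), df2 = (N−k)(m−1). With m = 2 and ρ = 0.5 (both assumed, neither stated): λ = 0.09 × 48 × 2/0.5 = 17.28, df = 2 and 45, power 0.958. So N = 48 is reproduced, for a single test at 0.05. (With m = 3 and the same ρ, 48 gives 0.988.)

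**2. Counting primary scores (section 2.3).**
- Cognitive, 11: CVLT-II immediate and delayed recall; BVMT-R immediate and delayed recall; SDMT; BJLO; COWAT; D-KEFS sorting and point scores; PASAT 3 s and 2 s.
- Gait and balance, 4: T25FW, 6MWT, Tinetti total, Berg.
- Total 15, or 30 tests over T1 and T2.
- Low count: one score for each of the seven cognitive tests plus three gait or balance measures = 10, or 20 tests.

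**3. Chance of at least one false-positive ANOVA with no true difference.** Under independence it is 1 − 0.95ⁿ. The correlated figures come from simulation with 20 patients per arm and equal correlations between scores. The article gives no correlations, so all of them are assumptions. Repeat runs differed by up to about 0.02.

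| Reading | Tests | Independent | Correlated (assumed) |
|---|---|---|---|
| 15 scores, T1 and T2 | 30 | 0.785 | 0.54–0.68 (scores 0.3–0.5, visits 0.5–0.7) |
| 11 cognitive scores, T1 and T2 | 22 | 0.676 | 0.47–0.60 (same) |
| 10 scores, T1 and T2 | 20 | 0.642 | 0.38–0.55 (scores 0.3–0.6, visits 0.6–0.8) |
| 15 scores, T1 only | 15 | 0.537 | 0.37–0.48 (scores 0.3–0.5) |
| 15 scores, one interaction test each | 15 | 0.537 | 0.34–0.48 (scores 0.3–0.6) |
| 10 scores, one visit | 10 | 0.401 | about 0.27 (scores 0.6) |

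These rows count only comparisons between arms; the within-group ANOVAs in each arm are extra.

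**4. The comparison in primary objective 2 (Reha 2 against Reha 1).** The article gives no pairwise effect size. If f = 0.30 is read as a between-group effect at one visit, with these two arms at the extremes and Reha 3 midway, then f = d/√6, so d = 0.30 × 2.449 = 0.735. With 20 per arm the noncentrality is 0.735 × √(20/2) = 2.324. On the pooled error (57 df), two-sided power is:
- at 0.05 as a single contrast: 0.63
- at 0.016 without an omnibus gate: 0.44
- at 0.016 after a significant omnibus test: 0.44

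The fall from 0.63 to 0.44 is due to the 0.016 threshold. The gate takes almost nothing beyond it.

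**The case against.** Several counter-arguments have weight.

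- **The motor outcomes belong in the trial's aim.** The abstract speaks of both cognitive and motor efficiency, and the discussion expects a double benefit. A reader might infer that memory is the only primary objective and that the motor primaries contradict it. Section 2.1 does not support that: memory is the second of two primary objectives. What stands is the lack of any ranking.
- **T2 may not be meant as primary.** Section 2.1 makes the six-month effects secondary, and the sentence on T1 and T2 covers primary and secondary outcomes alike. At T1 alone the correlated figures are below one half.
- **Section 4.1 names no ANOVA for gait or balance.** The 0.05 level reaches those scores only because it applies throughout the study. The cognitive scores alone give 0.47–0.60, on both sides of one half.
- **The sample size is for an interaction test,** which suggests one omnibus test per score and lowers the error further.
- **This is a condensed article.** A detailed testing hierarchy may properly sit in an analysis plan that is not shown, and its absence is no fault. But the article does state the primary set, the error level and where the correction applies, and those stated rules are what inflate the error.

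These points narrow the size of the problem. None brings the error near 0.05: the lowest figure, about 0.27, is still more than five times the nominal level.

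**Conclusion.** The point holds. Sections 4.1 and 4.2 together leave error uncontrolled across about 10 to 15 primary scores and up to 30 tests. The chance of at least one false-positive primary ANOVA is roughly 0.27 to 0.79, depending on the number of scores, on whether T2 counts, and on the assumed correlations.

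Two stronger conclusions are tempting and should not be drawn. One is that a false primary success is more likely than not. That is true for 15 scores at both visits under the moderate correlations tried, but not at T1 alone with correlated scores or with fewer, highly correlated scores. The other is that the planned memory comparison is penalised twice, by the omnibus test and then by 0.016. Under the assumed d = 0.735, power with the 0.016 threshold is 0.44 with or without the gate.

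**What to change.** Change sections 4.1 and 4.2 before any outcome data are seen:

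1. Name one memory score at T1 as the primary endpoint for primary objective 2, Reha 2 against Reha 1. CVLT-II total immediate recall is one candidate; another memory score of the sponsor's choice would serve equally.
2. Place one gait or balance measure at T1 next, either in a fixed testing order or as a co-primary with Holm adjustment.
3. Make all other scores, and T2, secondary, and claim no primary success from them. T2 as secondary agrees with section 2.1.
4. If the sponsor prefers to keep every score primary, apply Holm across the whole primary family.

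The textual change is small and needs no new assessments, but it has two costs. Other scores can no longer be claimed as primary. The power statement must also be rewritten for the named test: a single pairwise contrast with 20 per arm has power of about 0.63 under the assumed d = 0.735, far from the stated 0.95. Keeping all scores primary costs power too. Holm's first step over 30 tests is 0.05/30 = 0.00167, at which the interaction test (f = 0.30, ρ = 0.5) has power 0.67 at N = 48 and 0.83 at N = 60 with two measurements, or 0.85 and 0.95 with three.

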## 5. Ethics and Dissemination

This study involving human participants has been reviewed and approved by I.R.C.C.S “Santa Lucia” Foundation Ethics Committee (CE/PROG. 698; 26 July 2018). All the participants will provide written informed consent to participate in this study.

## 6. Discussion

The present study will have the benefit of comparing three rehabilitation training sessions with a specific focus on cognitive outcomes. To date, the possible option for the management of cognitive dysfunctions in MS is CR, applied separately or as a part of a multimodal program involving also MR. However, in clinical practice, multimodal programs are very infrequent and patients with MS are primarily treated via pharmacological approach and subsequently via motor exercise training (physiotherapy). CR still remains poorly accessible for MS patients.

On the other hand, dual-task studies have shown how motor and cognitive skills are closely associated [57,58]. For example, during the execution of specific motor exercises, the subject automatically activates the processes of planning, control and coordination (executive functions) which, in turn, we know are connected to memory functions. It is, therefore, possible that physiotherapy exercises favor an improvement in memory performance indirectly, by strengthening the executive functions associated with memory. In fact, the SNC should not be thought of as a set of independent modules, but as a network or a set of networks closely linked to each other. The brain areas are richly connected from an anatomical and functional point of view: therefore, by activating, for example, the motor cortex with physiotherapy exercises, it cannot be excluded that neuronal activity in the involved brain areas may indirectly enhance memory functioning. Therefore, we should consider motor and cognitive skills only apparently independent.

In this regard, one study reported significant memory improvements and concomitant increases in hippocampal volume following aerobic training in two people with MS and memory impairment [59]. On the other hand, the execution of specific memory exercises could reduce motor disabilities by the indirect action on the relative brain circuits.

As a consequence, we could expect that the combined rehabilitation (Reha 2) would allow a double advantage (both at a cognitive and motor level), thus ensuring greater effectiveness for the patient and a lower amount of time and resources.

Therefore, through this study, we aim to verify the hypothesis according to which combined rehabilitation intervention may be the best strategy to be used in MS patients having both motor and cognitive disabilities. We expect that a combined rehabilitation approach can bring a wider advantage as it may allow the enhancement of motor and cognitive skills at the same time.

Finally, by comparing the three rehabilitation approaches, we could even expect to highlight how the combined rehabilitation intervention favors an improvement in memory performance even higher than the CR alone.

If these results are reached, a change in clinical practice could be suggested: the combination of the two approaches in the same training with a reduction in time and costs for national health systems and a double advantage for MS patients.

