## Abstract

MS clinical features vary between patients. In approximately 60% of cases, cognitive deficits are associated with motor disabilities, with consequences on both walking and maintaining balance and cognitive efficiency. Multimodal programs are very infrequent for MS patients and cognitive rehabilitation is not provided by the Italian health system, which only favors access to motor rehabilitation. Dual-task studies showed how motor and cognitive skills are closely associated. Therefore, physiotherapy exercises may favor an indirect improvement in cognition. The aim of this study is to understand which rehabilitative approach may increase both cognitive and motor efficiency, avoiding the waste of time and resources. In this multi-site single-blind parallel controlled clinical trial, we will compare three rehabilitative approaches: cognitive training, motor training and combined cognitive–motor training. We also aim to evaluate: whether self-perception and objective improvement correspond; the impact of each rehabilitation program on patients’ QoL, mood and self-perception; and long-term effects. A total of 60 patients will be randomly assigned to one of the three treatments for two 45-min sessions/week for 12 weeks. All participants will undergo a complete cognitive, motor, clinical assessment together with mood, self-perception, and QoL questionnaires before, immediately after and 6 months after the training period.

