For the 12 weeks following randomization, each patient will undergo one of three rehabilitation programs:Reha 1: is composed by a computerized cognitive rehabilitation training using four sessions of the verbal memory set of the RehaCom program [15,16,17,18,19,20,21,22,23]. Each patient will carry out two 45-min sessions/week for 12 weeks;Reha 2: is composed by a combined rehabilitation program with the use of the four verbal memory sessions of RehaCom together with a motor rehabilitation program. Each patient will carry out one 45-min session of cognitive rehabilitation and one 45-min session of motor rehabilitation each week for 12 weeks;Reha 3: is composed of two 45-min sessions of motor rehabilitation training each week for a total duration of 12 weeks.

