○The California Verbal Learning Test-II (measurement of verbal learning and memory; CVLT-II) [28,29] requires the learning of a 16 words list (made up of 4 words from four different categories) read by the examiner across five trials. After each trial the subject has to recall as many words as possible in any order; the number of words correctly recalled for each trial is recorded. The total Immediate Recall (IR) score is the sum of the words correctly recalled across the five trials, ranging from 0 to 80. After having performed some interference tests the patient has to repeat the previously learned words (Delayed Recall; DR).○The Brief Visuospatial Memory Test—Revised (visuospatial memory test; BVMT-R) [30] consists of three consecutive trials in which the subject views for 10 s a display of six non-iconic figures, arranged in a 2 × 3 matrix. After that the subject has to reproduce each figure in the correct locations on the page. Patient is asked to reproduce the figures again after a 25-min interval without any further exposure to the stimuli. Scoring is based on the subject’s reproduction accuracy and location of each figure [31]. Each figure reproduced can receive 0 to 2 points score [32]. The Immediate Recall (IR) corresponded to the scores’ sum obtained across the three trials while the Delayed Recall (DR) is the score obtained in the 25-min delayed trial. The BVMT-R offers six equivalent alternative forms [33].○The Symbol Digit Modalities Test (information processing speed; SDMT; oral version) features a series of nine symbols, each of which is paired with a single-digit number in a pattern at the top of a sheet. The rest of the page has a pseudo-randomized sequence of these symbols. The patient is asked to say the digit associated with each symbol as quickly as possible in 90 s. The SDMT was originally designed for both written or oral responses, but the expert group recommended oral administration with MS patients to minimize complaints due to upper limb weakness or incoordination. The dependent variable is the total number of correct answers in 90 s [33,34].○The Benton Judgment of Line Orientation test (measures the accuracy of spatial orientation judgments; BJLO) [35] requires subjects to identify the angle defined by two stimulus lines among those reported in a visual series of lines spanning 180 degrees. The dependent variable of the BJLO is the total number of correct answers [33].○The Controlled Oral Word Association Test (measure of phonemic fluency; COWAT) gives subjects three 1-min time intervals each to generate as many words as possible beginning with three different input letters. Given that the subject’s performance is strongly influenced by the efficiency and speed of the search into one’s own lexicon, the COWAT cannot be considered a test of “pure” language. The total score is the total number of words generated in all three tests. Two equivalent alternative forms are available [33].○The Delis–Kaplan Executive Function System Sorting Test (D-KEFS ST) is a composite measure of: concept formation skills, specific problem-solving skills for verbal/non-verbal aspects and ability to explain the abstract ordering of concepts [36]. It is able to explore reasoning, categorization skills, problem solving, abstraction, flexibility of thought and conceptual training skills, and it also provides good validity [37] and adequate reliability [38]. The test involves the presentation of six mixed cardstocks having different perceptual and semantic characteristics. The participant is asked to divide the cards into two groups (categorization), with three cards each, based on objective criteria and to describe the concepts used to generate each categorization (description). Each of the two sets of cards has a maximum of eight types of categories: three based on the semantic meaning of the printed words and five based on the cards’ visuo-spatial characteristics or patterns. The participant has a maximum of 4 min (for each set of cards) to find as many categorizations as possible [39]. The Sorting Score (SS) represents the total number of correct categorizations made by the subject; the Point Score (PS) represents the quality of the description (classifications) made for all the SS.○The Paced Auditory Serial Addition Test in 3 and 2 s versions (measure of working memory; PASAT). It takes 20 min to administer and has adequate sensitivity and specificity (approximately 75% and 90%, respectively) in discriminating compromised patients from intact ones [40,41] In this test the patients asks some digit numbers each 3 or 2 s. He/she is asked to sum the number just said with the previous and say each time the correct sum.

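### With every arm trained, significance tests of change within an arm cannot show that a programme works; efficacy conclusions should rest on between-arm contrasts

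*Protocol article*

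**What the plan says.** The Abstract describes a comparison among active treatments: "we will compare three rehabilitative approaches: cognitive training, motor training and combined cognitive–motor training". Section 2.1 gives each arm two 45-minute sessions a week for 12 weeks. Reha 1 has two memory sessions, Reha 2 has one memory and one motor session, and Reha 3 "is composed of two 45-min sessions of motor rehabilitation training each week for a total duration of 12 weeks". There is no untrained, waiting-list or sham arm.

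The primary objectives in section 2.1 are comparative. A secondary objective is not: "Evaluate the impact of each rehabilitation program" on overall disability. The Abstract likewise sets out to evaluate "the impact of each rehabilitation program on patients’ QoL, mood and self-perception; and long-term effects". The Discussion adds, as a possible mechanism and not as an objective: "It is, therefore, possible that physiotherapy exercises favor an improvement in memory performance indirectly, by strengthening the executive functions associated with memory".

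Section 4.1 plans two families of analysis. For the within-group family it says: "These statistical analyses will be aimed at evaluating any improvement in patients’ cognitive performance". T0 is compared with T1 and T2 inside each arm by repeated measures ANOVA at p<0.05, then by post hoc tests at p<0.016. The same analysis is applied to anxiety, depression, self-perceived cognitive deficit and perceived disability. The between-group family compares the arms at T0, T1 and T2 on the same variables. The sample size is set on the within-between interaction.

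One safeguard against practice effects is stated in section 2.1: "each patient will undergo an overall re-evaluation (T1) with parallel forms of the tools used at T0".

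**The concern.** The article gives an uncontrolled before-after test the job of deciding whether an arm improved. A significant rise in one arm is the sum of any training effect and everything else that moves scores between visits: familiarity with the tests, regression to the mean, expectation on the self-report scales, residual recovery from a relapse more than 3 months before enrolment, and progression in patients with an SP course over the roughly 9 months from T0 to T2. Most of these push scores up. Progression pushes them down and could hide a real gain.

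The risk is sharpest in the motor-only arm. A significant memory rise there would fit the mechanism in the Discussion and could be reported as a cognitive benefit of physiotherapy, in a paper that says its results could suggest a change in clinical practice. The same applies to a motor rise in the cognitive-only arm, since the Discussion also raises the reverse pathway.

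**Working it through.** **1. What the plan's own sample size supports.** Inputs from section 4.1: effect size 0.30 (read as Cohen's f), alpha 0.05, power above 0.95, 3 groups, stated minimum N = 48. Assumed, because not stated: correlation 0.5, no sphericity correction, and m = 2 occasions. For the within-between interaction, λ = f²·N·m/(1−ρ), df1 = (k−1)(m−1), df2 = (N−k)(m−1).

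- N = 48: λ = 0.09 × 48 × 2 / 0.5 = 17.28, df 2 and 45, power 0.958.
- N = 45: λ = 16.2, df 2 and 42, power 0.945.

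So 48 is reproduced as the smallest balanced N. (With three occasions, 39 would suffice, with power 0.962.) The figure powers the group-by-time interaction, a comparison among active arms. It says nothing about one arm's own effect.

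**2. What each contrast contains.** Let P be change common to all arms, C(j) the effect of j weekly memory sessions on memory, and M(j) that of j weekly motor sessions, with M(1) including any benefit of combining the two.

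- Change within Reha 3 = P + M(2)
- Change within Reha 1 = P + C(2)
- Reha 2 − Reha 1 = M(1) − [C(2) − C(1)]
- Reha 3 − Reha 1 = M(2) − C(2)

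P stays in every within-arm change and cancels in every between-arm difference.

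**3. How often P alone gives significance.** Set all training effects to zero, n = 20 in the arm, and visit means 0, g, g in SD units with equal correlation r between visits. The values of g and r are assumptions; the article gives neither.

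ANOVA: the squared deviations of (0, g, g) about their mean sum to 2g²/3, so λ = n(2g²/3)/(1−r), df 2 and 38, critical F = 3.245. For g = 0.3 and r = 0.7: λ = 20 × 0.06 / 0.3 = 4.0, rejection 0.39.

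Paired T0-T1 test at 0.016: noncentrality = g√n / √(2(1−r)), df 19, critical |t| = 2.644. For g = 0.3 and r = 0.7: 0.3 × 4.472 / 0.775 = 1.73, rejection 0.21.

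| g | r | ANOVA, p<0.05 | T0-T1 test, p<0.016 |
|---|---|---|---|
| 0.2 | 0.5 | 0.13 | 0.06 |
| 0.2 | 0.7 | 0.19 | 0.09 |
| 0.2 | 0.8 | 0.27 | 0.14 |
| 0.3 | 0.5 | 0.25 | 0.12 |
| 0.3 | 0.7 | 0.39 | 0.21 |
| 0.3 | 0.8 | 0.55 | 0.33 |
| 0.4 | 0.5 | 0.41 | 0.23 |
| 0.4 | 0.7 | 0.63 | 0.39 |
| 0.4 | 0.8 | 0.81 | 0.58 |

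The rates are per score. The paired rate is for that test alone; the plan runs it only after a significant ANOVA, so the two-step rate for that pair is no higher.

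**4. The same drift in the group-by-time test.** In simulation with 20 per arm, r = 0.7 and a rise of 0.5 SD common to all arms, the interaction rejects in 4.8% of trials, and in 5.0% with no rise.

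**The case against.** The strongest reply is that this is a legitimate active-comparator trial. Its primary objectives, including combined against cognitive training alone, are between-arm questions, and the randomised comparisons are unaffected by a common retest gain. Between-group analyses are already planned for the same variables. All of that stands. It limits the point to the within-arm tests and the each-programme wording.

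Three stronger readings are tempting, and the article does not support them.

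- **That physiotherapy improving memory is a stated aim.** It is not a listed objective. The Abstract and Discussion give it as hedged rationale.
- **That the design can never show transfer.** By step 2, if Reha 2 beats Reha 1 on memory, and a second weekly memory session does not harm, then M(1) must be positive. Reha 3 beating Reha 1 would point the same way if memory training itself does not harm. That would be randomised evidence, and conservative, because the motor effect must overcome the memory training it replaces.
- **That form order is not counterbalanced, so form difficulty is tied to visit.** The article is silent on order, and a condensed article may leave that to the full protocol. For COWAT it says "Two equivalent alternative forms are available" against three visits, but it calls those forms equivalent, COWAT measures fluency rather than memory, and the BVMT-R, a memory test, has six forms.

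The safeguards also deserve credit. Parallel forms reduce item learning. Table 1 excludes relapse or steroids in the prior 3 months, and relapse or MRI activity during treatment. They do not remove general test familiarity, regression to the mean, expectation or slow progression, and parallel forms do little for questionnaires. Finally, the size depends on assumed gains: at 0.2 SD and r = 0.5 the excess is modest (13% for the ANOVA, 6% for the post hoc test).

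**Conclusion.** The point holds for the within-arm analyses. Followed as written, section 4.1 can declare that a programme improved its patients from score drift alone. With no training effect, an assumed persistent gain of 0.2-0.4 SD, r of 0.5-0.8, 20 patients per arm and equal correlations, the ANOVA rejects in about 13-81% of trials per score against a nominal 5%, and the T0-T1 post hoc test in about 6-58% against a nominal 1.6%. A gain shared by all arms leaves the group-by-time test near 5%. The direction of the bias follows from the design; its size rests on the assumptions. The trial can still rank the three programmes. This should be changed, but it does not undermine the primary randomised comparisons.

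**What to change.** In sections 2.1 and 4.1:

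1. State that every efficacy conclusion rests on group-by-time (between-arm) contrasts, and define the impact of each programme as its impact relative to the other two.
2. Label the within-arm T0-T1-T2 tests descriptive.
3. State that a memory rise within Reha 3 alone, or a gait or balance rise within Reha 1 alone, is not evidence of transfer, whereas superiority of Reha 2 or Reha 3 over Reha 1 on memory would be randomised, conservative evidence of a motor contribution.

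The cost is wording only. No patients, visits or tests are added, and the sample size already rests on the interaction: at the plan's f of 0.30 and the assumptions in step 1, 60 patients give power 0.987 for the overall interaction test (individual pairwise contrasts will have less). The price is that the trial gives up absolute claims about any single programme; those would need an untrained or waiting-list comparator.
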